### Analysis Plan for Secondary Aims

For neurohormonal markers: BNP, TNF-alpha, c-reactive protein, and norepinephrine, two-sample Wilcoxon rank-sum tests will also be used to compare distribution of change from baseline to 12 weeks between intervention and control groups.

Scores on other quality of life, mood, and exercise self-efficacy assessments will be analyzed using similar tests: Wilcoxon rank-sum, comparing the change from baseline to 12 weeks between treatment and control groups. In addition, we will use linear regression models using primary study outcomes (change in six-minute walk, peak VO2, and MLHF score) as dependent variables and scores on these psychosocial assessments as predictors to examine whether clinical outcome is associated with quality-of-life, mood, or self-efficacy. Separate models will be developed for each primary outcome. In the Tai Chi intervention group, we will also describe patient attendance at classes and compliance with home practice and determine whether compliance is associated with either baseline exercise self-efficacy or a positive change in exercise self-efficacy.

Medical utilization costs of the two groups will be compared using Wilcoxon rank-sum tests, examining cost components (outpatient visits, telephone contacts, hospitalizations, radiology and laboratory tests, procedures, and medications) separately and in total. We will also use linear regression models to adjust for baseline patient characteristics, such as sociodemographic variables (race) or clinical variables (co-morbidities and NYHA class).

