### Statistical Analysis and Power

Prior to analyzing the outcomes, we will compare the randomized groups with respect to baseline demographic, functional, and clinical variables as well as known prognostic factors (such as baseline NYHA class and baseline peak VO2) using chi-square and Fisher’s exact tests. Although we do not expect any differences with proper randomization, any significant imbalances (p<.05) will be adjusted for in the statistical analyses. All analyses will be performed on an intention-to-treat basis.

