## POSSIBLE BENEFITS

This study will increase our understanding of the potential benefits of a tailored 12-week Tai Chi program on functional and health-related quality of life in patients with chronic heart failure. Tai Chi has the potential to improve the physical functioning and quality of life for patients with living with congestive heart failure. This study will also enable us to better understand the mechanisms (physiologic and metabolic pathways and behavioral and psychosocial effects) underlying any benefits of Tai Chi. In addition, this study will provide data on the cost-effectiveness of Tai Chi as adjunctive therapy.

If such benefits are demonstrated, Tai Chi could represent a new adjunctive therapy for cardiac patients, which is not currently a part of standard care. Especially, in patients with heart failure who are difficult to engage in activity, a mind-body exercise form may be particularly appropriate and help to define optimal exercise protocols in this population. This study will also allow us to gain important knowledge regarding potential mechanisms of mind-body therapies that can be applied to other chronically ill populations where stress-related physiology plays an injurious role. Finally, we will offer all patients the benefit of participating in Tai Chi, regardless of their assign study group. For patients assigned to the education control group, we will offer free Tai Chi classes for 12 weeks after participating in the study.

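### The regressions of the primary outcomes on psychosocial scores name no treatment term and no score timing; with change or 12-week scores, a treatment effect on both variables can show up as an association that does not exist within arms

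*Protocol*

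**What the plan says.** The Protocol, under Analysis Plan for Secondary Aims, first compares the psychosocial scores between arms by rank-sum test, "comparing the change from baseline to 12 weeks between treatment and control groups". It then adds a regression: "In addition, we will use linear regression models using primary study outcomes (change in six-minute walk, peak VO2, and MLHF score) as dependent variables", with "scores on these psychosocial assessments as predictors to examine whether clinical outcome is associated with quality-of-life, mood, or self-efficacy". The models are divided by outcome only: "Separate models will be developed for each primary outcome".

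Three neighbouring statements help in reading this.

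- The next analysis is limited to one arm ("In the Tai Chi intervention group, we will also describe patient attendance at classes and compliance with home practice") and specifies its score ("either baseline exercise self-efficacy or a positive change in exercise self-efficacy"). The regression does neither.
- The cost regression in the same section says what it adjusts for. This one names no adjustment.
- The general rule under Statistical Analysis and Power, "any significant imbalances (p<.05) will be adjusted for in the statistical analyses", concerns baseline differences, not treatment.

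The plain reading is therefore a model on both arms together with psychosocial scores as its only named predictors. Which visit the scores come from is not stated. Because the sentence before it deals with change to 12 weeks, change scores are the natural reading, but not the only one.

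**The concern.** The trial is built on the expectation that Tai Chi shifts the outcomes, and the Emotional Status/Mood section cites Tai Chi studies in which POMS mood improved. If treatment moves an outcome and a score, the two arms form two clouds of points displaced in both directions. A single line through both clouds then has a slope even when outcome and score are unrelated inside each cloud.

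What is at stake is interpretation. The Possible Benefits section says "This study will also enable us to better understand the mechanisms", and lists psychosocial effects among them. A significant coefficient from a pooled model could be taken to mean that patients whose mood or self-efficacy improved more also gained more exercise capacity, when it may reflect only that one arm did better on both.

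**Working it through.** The Protocol gives no figure for this regression, so there is none to reproduce. The check asks how often a pooled model gives p<0.05 when there is no within-arm relation.

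**Inputs from the Protocol (Sample Size Justification)**

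- 50 patients per arm and 20% dropout: 50 × 0.80 = 40 per arm, N = 80.
- Standardised outcome effect d1: peak VO2 1.5/2.1 = 0.714; MLHF 12.5/17 = 0.735; walk 240/317 = 0.757. The pilot SDs of change are taken as within-arm SDs.

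**Assumed:** the standardised treatment effect on the psychosocial score, d2, is not in the Protocol and is varied from 0.2 to 1.0. The test is two-sided at 5%, one predictor at a time. Effects are absolute sizes; their direction changes only the sign of r.

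**Formula.** With 1:1 allocation and no within-arm relation, the pooled covariance is d1·d2/4 and the pooled variances are 1 + d1²/4 and 1 + d2²/4, so

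r = (d1·d2/4) / √[(1 + d1²/4)(1 + d2²/4)].

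The chance of p<0.05 follows from Fisher's z: atanh(r)·√(N − 3), compared with ±1.96.

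**Worked case,** peak VO2 with d2 = 0.5: the numerator is 0.714 × 0.5/4 = 0.0893 and the denominator is √(1.1275 × 1.0625) = 1.0945, so r = 0.082. Then atanh(r)·√77 is about 0.72, and the chance of falling beyond ±1.96 is 11.1%.

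**Results at N = 80 (induced r, chance of p<0.05)**

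| d2 (assumed) | Peak VO2 | MLHF | Walk |
|---|---|---|---|
| 0.2 | 0.033, 6.0% | 0.034, 6.0% | 0.035, 6.1% |
| 0.5 | 0.082, 11.1% | 0.084, 11.4% | 0.086, 11.7% |
| 0.8 | 0.125, 19.7% | 0.128, 20.4% | 0.131, 21.3% |
| 1.0 | 0.150, 26.5% | 0.154, 27.6% | 0.158, 28.9% |

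With no dropout (N = 100) the range is about 6% to 35%.

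**Simulation check** (6,000 runs per case, 40 per arm):

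- No arm term, post-baseline score: 6.3%, 11.2% and 19.9% for peak VO2 at d2 = 0.2, 0.5 and 0.8; 29.4% for the walk at d2 = 1.0. These agree with the formula.
- Arm term included: 4.9% to 5.4% in every case.
- Baseline score as predictor, no arm term: 4.6% to 5.6%. Randomised arm is independent of a baseline score, so nothing is induced.
- Treatment moving only one of the two variables, no arm term: 5.1% (outcome only) and 4.6% (score only).

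**The case against.** The strongest reply is that the Protocol nowhere says that the arms are pooled or that treatment is left out. It names the predictors of interest, says that models will be developed, and may leave the full covariate list to a statistical analysis plan that is not seen here. This stands in part. Deliberate exclusion of arm cannot be inferred from silence. But the sentence does give a predictor list, without the arm restriction or the adjustment that its neighbours carry, so an analyst who follows it literally would fit the pooled model.

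Second, the problem depends on score timing, which is not fixed. This stands fully: with baseline scores the concern disappears.

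Third, the stated aim is association, not mediation. This also stands. If treatment moves both variables, the marginal association is real, and an arm-adjusted model answers a different question. What the marginal coefficient cannot support is a within-arm reading.

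Fourth, the link to mechanism is loose. Possible Benefits is general text and does not say that any mechanism conclusion will rest on this regression. The between-arm comparisons of outcomes and scores would also show a reader whether both had shifted.

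**Conclusion.** The point holds as a conditional one. With change or 12-week scores, and a treatment effect on both outcome and score, the regression as written can show an association that has no within-arm counterpart. At the design effects and 40 completers per arm, the chance per predictor is about 6% to 29% over assumed score effects of 0.2 to 1.0 SD, against about 5% with an arm term. The induced correlation is small, about 0.03 to 0.16.

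A reader might infer more than the Protocol supports:

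- **That a spurious association will appear.** It needs both effects and post-baseline scores, and even then it is significant in a minority of trials over the range examined.
- **That the rate is higher still.** Setting both effects at 1 SD gives about 44%, but 1 SD exceeds every outcome effect the trial was designed on. The Protocol describes its walk and MLHF differences as half those seen in the pilot; a pilot-sized walk effect (480/317 = 1.51 SD) would give about 25% at a score effect of 0.5 SD, but that is not the planning assumption.
- **That quality-of-life predictors of MLHF change, or the lack of a baseline-outcome or score-by-arm term, are errors.** These are modelling preferences; nothing in the Protocol makes the present choice wrong.
- **That the trial's main result is affected.** The primary rank-sum comparisons do not use these models.

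**What to change.** In Analysis Plan for Secondary Aims, state whether the psychosocial predictors are baseline, 12-week or change scores, and include randomised arm as a covariate in each of the three sets of models, so that the coefficient is read as an association within arm.

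This changes analysis wording only and needs no new data. It costs one residual degree of freedom (78 to 77 with one predictor and 80 patients). The coefficient will also no longer contain the treatment-driven part of the association. If that marginal quantity is wanted too, it can be reported beside the adjusted one and labelled as such.

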### Intervention

We will utilize the same Tai Chi protocol that we developed, refined, and successfully employed in our pilot study.This intervention, broadly based on a Tai Chi program developed by Wolf and colleagues for use in trials with elderly patients17 emphasizes essential Tai Chi movements that are both easily comprehensible and can be done repetitively in a flowing manner. The five chosen Tai Chi movements––*‘raising the power’*, *‘withdraw and push’*, *'grasp the sparrow's tail'*, *‘brush knee twist step’*, and *‘wave hand like clouds’* –– are based on the traditional Cheng Man-Ch’ing’s Yang-style short form. In addition to these five formal movements, the intervention includes a complementary set of traditional Tai Chi warm-up exercises and a 2 minute cool-down period with breathing exercises. These focus on loosening up the physical body, incorporating mindfulness and imagery into movement, increasing awareness of breathing and promoting overall relaxation of body and mind. This intervention was developed by [name] who has more than 25 years of Tai Chi experience.

Two senior Tai Chi students and certified graduates of a 2.5 year instructor training program developed by [name] will administer the Tai Chi intervention under [name] direction. Some instructors taught classes for the pilot study and have already gained experience working with a frail cardiac population and appreciate the unique set of challenges this population may bring. Prior to the start of the trial, [name] will conduct a series of trainings to review the protocol. Video analysis of mock group sessions will be used to ensure consistent application of the protocol.

Tai Chi classes will be conducted twice weekly for one hour each for 3 months (identical to the intervention used in our pilot study). Many prior Tai Chi trials have demonstrated clinical changes using a similar-length intervention.

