## Medical Utilization and Collection of Cost Data

Medical record, interview data, and automated utilization data will be used to document patients’ use of health care during the study period. We will collect information on visits to healthcare providers, telephone contact with health care providers, use of prescription and over the counter medications, use of radiology and laboratory tests, hospitalizations, and other invasive or non-invasive cardiac procedures (e.g., cardiac catheterizations, cardioversion, pacemaker implantation). We will track both insurance payments and out-of-pocket expenses.

We will compare the health care resources used by patients randomized to education attention control to resources use by patients randomized to Tai Chi. Information will be obtained through patient self-report. Studies that have primarily relied on patient interview have found that the average error in self-reported utilization is small.97 However, for those patients referred from the BIDMC, we will also utilize the hospital database and online medical record system that tracks office visits, telephone contacts, hospitalizations, emergency room visits, radiology and laboratory tests, procedures, and prescription medications. This will allow us to check self-reported utilization by comparing self-report data with that captured through the hospital database. We will not track these electronic data at any other site since database systems of those hospitals are not fully integrated online, and thus, would not yield comparable information.97 A standardized Medicare Fee Schedule will be used to assign an estimate of costs in dollars to hospitalizations and visits to physicians and nurses. The fee schedule also will assign cost estimates to prescription medications, lab and radiology tests, and cardiac procedures. Costs of over the counter medications will be estimated based on wholesale costs and average national dispensing costs.

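### The lead cost comparison ranks health care costs and leaves out class delivery, so as written it does not deliver the promised cost-effectiveness data

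*Protocol*

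**What the plan says.** **The promise.** The protocol's Possible Benefits section states that "this study will provide data on the cost-effectiveness of Tai Chi as adjunctive therapy".

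**The lead comparison.** Under Analysis Plan for Secondary Aims: "Medical utilization costs of the two groups will be compared using Wilcoxon rank-sum tests, examining cost components". The components are then listed: "outpatient visits, telephone contacts, hospitalizations, radiology and laboratory tests, procedures, and medications) separately and in total".

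**A second method.** The next sentence adds: "We will also use linear regression models to adjust for baseline patient characteristics, such as sociodemographic variables (race) or clinical variables". It does not say whether costs enter in dollars or transformed.

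**What is costed.** Under Medical Utilization and Collection of Cost Data: "We will collect information on visits to healthcare providers, telephone contact with health care providers, use of prescription and over the counter medications", followed by tests, admissions and cardiac procedures. On payments: "We will track both insurance payments and out-of-pocket expenses". On unit costs: "A standardized Medicare Fee Schedule will be used to assign an estimate of costs in dollars to hospitalizations and visits to physicians and nurses". Prescriptions, tests and procedures are priced from the same source. None of these lists contains the study classes.

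**What the classes consist of.** Under Intervention: "Tai Chi classes will be conducted twice weekly for one hour each for 3 months". Trained instructors teach them, with a nurse or a staff member certified in basic life support present each time. The control sessions are also twice weekly and are run by the study nurse. Attendance is recorded in both arms.

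**The concern.** A cost-effectiveness statement needs an incremental cost: the difference in arithmetic mean cost per patient, because only the mean multiplies up to a total budget. A rank-sum test asks whether a patient drawn from one arm tends to cost more than a patient drawn from the other. When a few admissions carry much of the cost, the ranks mostly follow the many patients who have only routine costs, and the two questions can have different answers.

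The second gap does not depend on the test. The study supplies the classes, so their cost does not appear in insurance payments or patients' own expenses. A total built from the listed components therefore leaves out the cost of the intervention whose value is to be judged.

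At stake is the cost conclusion. A rank result on utilization-only costs could be reported as economic evidence for or against Tai Chi when it does not estimate the relevant quantity.

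**Working it through.** The protocol gives no costs, cost SD, admission rates, class sizes or staff rates, so it has no figure of its own to reproduce. Every dollar amount, admission rate and class size below is an assumption. From the protocol come the arm size (50), the 20% dropout (50 × 0.8 = 40 remaining) and the class schedule.

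**1. Can ranks and means disagree at this sample size?** Fixed example, 50 per arm:
- Arm A: 48 patients at $1,200 and 2 at $10,000. Mean = (57,600 + 20,000)/50 = $1,552.
- Arm B: 42 patients at $1,000 and 8 at $10,000. Mean = (42,000 + 80,000)/50 = $2,440.
- Mean difference A − B = −$888, so A is cheaper.
- Pairs in which A costs more, counting ties as one half: 48 × 42 + 2 × 42 + ½ × 2 × 8 = 2,016 + 84 + 8 = 2,108. P(A > B) = 2,108/2,500 = 0.84.
- Rank-sum p ≈ 6 × 10⁻¹¹, in the direction of A being dearer.

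**2. How often, once routine costs vary?** Simulation of 10,000 trials per setting: log-normal routine cost (log-SD 0.8) plus an occasional admission averaging $10,000. True mean difference = (median A − median B) × exp(0.8²/2) + (admission rate A − admission rate B) × 10,000, with exp(0.32) = 1.377. For the last row: 500 × 1.377 − 1,000 = −$311.

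| Routine median, A / B | Admitted, A / B | True mean difference | Rank direction opposite (n = 40 / 50 per arm) | Opposite with p < 0.05 (n = 40 / 50 per arm) |
|---|---|---|---|---|
| $1,000 / $1,000 | 5% / 15% | −$1,000 | 22.4% / 19.8% | 0.4% / 0.3% |
| $1,200 / $1,000 | 5% / 15% | −$725 | 52.5% / 53.9% | 2.7% / 3.0% |
| $1,200 / $1,000 | 10% / 15% | −$225 | 65.5% / 67.4% | 5.9% / 6.9% |
| $1,500 / $1,000 | 5% / 15% | −$311 | 85.0% / 87.9% | 18.0% / 21.6% |

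The result depends on routine costs running against admissions, and on how widely routine costs spread. In another assumed case, one arm has 44 patients with median routine cost $400 and 6 at $20,000; the other has 48 with median $500 and 2 at $20,000. The share of trials significant in the wrong direction falls from 98% at log-SD 0.2 to 64% at 0.3, 16% at 0.5 and 4% at 0.8.

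**3. How large is the omitted cost?** Sessions = 2 per week × 12 weeks = 24. Delivery cost per patient = 24 × staff cost per session / class size.
- Low: 24 × $50/12 = $100.
- High: 24 × $200/5 = $960.

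The net between-arm cost is the utilization difference plus (delivery cost A − delivery cost B). If A were the Tai Chi arm, a utilization saving of $311 would reverse once its classes cost more than $311 per patient above the control sessions.

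**The case against.** **The data are not lost.** A reader might infer that cost-effectiveness data cannot be obtained at all. The protocol does not support that. It plans linear regression of costs; on untransformed dollars with a group term, that gives an adjusted mean difference. Resource use is itemised with unit costs, and class delivery can be rebuilt from the schedule, staffing and attendance logs. This stands. However, the cost scale is not stated, and no sentence makes the mean difference the result to report.

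**The stated aim is narrower.** The cost sections speak of health care resources and utilization costs, and for that aim leaving out the classes is a choice of scope. The cost-effectiveness promise is a single sentence, and economic detail may sit in an analysis plan that is not at hand. This is fair as to missing detail. It does not answer the point that the protocol itself names the test, lists the costs, and promises a quantity that neither supplies.

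**The wrong sign is a corner case.** A reader might infer that the cost result will have the wrong sign. The simulations do not show this: with equal routine costs, a significant reversal occurs in under 1% of trials. The objection stands as to frequency. The rank test still does not estimate the mean difference in any setting.

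**Both arms have classes.** The sessions are time-matched, so much of the delivery cost may cancel between arms. This stands. Cancellation need not be complete, because Tai Chi classes have an instructor as well as attending staff, while the study nurse runs the control sessions.

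**Conclusion.** The point holds in a limited form. Followed as written, the lead cost analysis gives a rank comparison of utilization-only costs, which is not the quantity a cost-effectiveness statement needs.

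- **Ranks against means.** Disagreement in direction is possible at 40 to 50 patients per arm. In the simulated settings, significant reversals range from under 1% to about 22% of trials, depending on assumed costs that the protocol neither gives nor rules out.
- **Delivery cost.** The omission is certain on the text; its size is not. The $100 to $960 per patient is an assumed range for one arm. It would be wrong to read the whole amount as bias in the randomized comparison, where only the difference in delivery cost enters. The full Tai Chi cost counts when Tai Chi is judged as an addition to standard care, which is how Possible Benefits presents it.

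This concerns a secondary aim. It does not touch the three primary endpoints or the sample size.

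**What to change.** 1. Make the difference in arithmetic mean total cost per patient, with a bootstrap confidence interval, the lead cost comparison, and report components the same way. Keep the rank-sum tests as descriptive or supportive.
2. State that the regression models cost in dollars and includes treatment group. A generalized linear model with gamma errors is an option, not a requirement.
3. Add each arm's class delivery cost (instructor time, nurse or other attending staff time, materials) from study records and attendance logs. Show the total with and without it.
4. If the classes are not to be costed, limit the Possible Benefits sentence to health care utilization costs.

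The cost is a change of wording and a small tally of class costs. Intervals for mean cost will be wide in a trial of 100 patients and will look less decisive than a rank-sum p-value. No change to enrolment or outcome assessment is needed.
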